**Fig. 2 Fig2:**
[figure not shown]
Study flow diagram. Participants will be randomly assigned to either an exercise or stretching intervention program. AKS, Aging Kidney Study; AKETS, Aging Kidney and Exercise Training Study

### Intervention

#### Exercise intervention group

Participants assigned to the exercise training group participate in an individualized, progressive, multicomponent training program based on the official exercise guidelines of the Japanese Ministry of Health, Labour, and Welfare (https://www.mhlw.go.jp/content/000656460.pdf). The program includes aerobic, resistance, and balance training and is conducted either under supervision at the Medical Fitness Center Phoenix (Tsukuba, Ibaraki, Japan) or unsupervised at home. The participants are instructed to exercise at least three times per week for approximately 60 min per session, with at least one session per week performed under supervision. In addition to each exercise session, warm–up and cool–down activities for approximately 15 min are included. During supervised aerobic sessions, the participants perform 20 min activities using a treadmill or cycle ergometer at an intensity of 50–70% of their age–predicted maximum heart rate calculated using the Tanaka formula (i.e., 208 − 0.7 × age) [44], corresponding to a perceived exertion of “somewhat hard.” Supervised resistance training consists of five machine–based exercises—namely, chest press, seated rowing, leg press, leg curl, and leg extension. Each exercise is performed in 2–3 sets of 10–12 repetitions at 30–70% of the one–repetition maximum (1–RM). The exercise dose (i.e., load, repetitions, and sets) is progressively adjusted based on the participant’s adaptation. The exercise load for months 0–6 is determined using baseline 1–RM, whereas the exercise load for months 7–12 is based on reassessment at 6 months. In unsupervised sessions, participants are encouraged to engage in aerobic activities such as walking, bodyweight resistance exercises (e.g., squats and push–ups), and balance exercises (e.g., front lunges and heel raises). The heart rate is monitored and recorded in real time during all sessions using a wrist–worn device (Xiaomi Smart Band 9, Xiaomi Japan, Tokyo, Japan). To monitor adherence, the participants are required to complete a daily exercise training log documenting their pre–exercise blood pressure, subjective condition, exercise type, duration, and heart rate. Exercise training logs are collected monthly at the Medical Fitness Center Phoenix (Tsukuba, Ibaraki, Japan) and reviewed to assess compliance with the prescribed program. When necessary, follow–up support is provided via telephone or in–person meetings to encourage sustained engagement.

#### Stretching intervention group (Active control group)

To maintain participant motivation and ensure ethical requirements, an active control group is established and provided with a structured stretching intervention program. This program consists of 20 static stretching exercises targeting major muscle groups in the upper body, trunk, and lower body and is designed to minimize cardiovascular load by minimizing heart rate elevation. Following randomization, the participants attend an orientation session in which a certified instructor explains each stretch movement and the procedures for the logging activity. The stretching program is designed to be performed for 10–20 min per session. During the first six months, both the number of stretching exercises and the total session duration are progressively increased. The participants are instructed to perform stretching exercises at home at least three times per week. To monitor adherence, completed stretching logs are collected monthly and reviewed by study personnel.

#### Usual lifestyle group (Time control group)

Within the AKS cohort, a group of participants who are followed up without receiving any intervention is designated as the usual lifestyle (i.e., time control) group for this study. The participants who opt for the time control group are instructed to maintain their usual lifestyle habits and encouraged to participate in annual follow–up assessments.

### Measurements

This study covers four assessment points: baseline, midpoint (6 months), end of intervention (12 months), and follow–up (24 months). Except for magnetic resonance imaging (MRI) and maximal dynamic strength measurements, all assessments are performed at the University of Tsukuba. MRI scans and maximal dynamic strength measurements are scheduled to be performed at the National Institute of Advanced Industrial Science and Technology and Medical Fitness Center Phoenix. After laboratory assessments, the participants also undergo triaxial accelerometer measurements to assess their daily sedentary behavior and physical activity.

### Primary and secondary outcome measures

The primary outcome of this study is the annualized rate of change in eGFR (i.e., eGFR slope), expressed as mL/min/1.73 m² per year. Based on findings from a recent meta–analysis of RCTs, the eGFR slope is recognized as a reliable surrogate endpoint for tracking CKD development [45, 46]. Given that serum cystatin C levels are less influenced by physical activity and muscle mass than serum creatinine levels [47], serum cystatin C levels are used to calculate the eGFR and evaluate changes in kidney function. The eGFR slope is determined using a linear mixed–effects model with random intercepts [48].

The secondary outcomes include alterations in renal hemodynamics and oxygenation assessed using Doppler ultrasound imaging and MRI, glomerular and tubular damage biomarkers, cardiovascular function indices, such as arterial stiffness and endothelial function, blood– and urine–based markers of mineral and bone metabolism, body composition and bone density, muscle strength, cardiorespiratory fitness, physical performance, habitual dietary intake, sedentary behavior, physical activity, sleep quality, and mental health. The detailed measurement methods for the secondary outcomes are provided in the Supplementary Material.

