Several cross–sectional studies have reported that individuals with higher levels of physical activity and performance tend to have better kidney function [14–18]. Furthermore, longitudinal studies have demonstrated an independent association of physical activity and fitness with preventing CKD development and rapid kidney function decline [19–23]. Recent evidence from animal model studies also indicates the potential renoprotective effects of long–term exercise training in various CKD models [24–28]. These epidemiological and basic findings suggest that exercise training aimed at improving physical activity and fitness could be an effective strategy for preventing CKD development [29, 30]. However, it remains possible that declines in kidney function may lead to reduced muscle mass and impaired physical performance, subsequently resulting in lower physical activity levels (i.e., reverse causation). Indeed, evidence in humans from the limited number of randomized controlled trials (RCTs) investigating whether exercise training benefits kidney health has been inconsistent [31–34]. Therefore, the renoprotective effects of exercise training remain uncertain and controversial, highlighting the need for rigorously designed interventional studies to clarify causality.

The inconsistent findings from exercise–nephrology RCTs may stem from the possibility that kidney aging is irreversible and progresses slowly with significant individual variations. Thus, when investigating the effects of exercise training on kidney health, within–group (intra–individual) comparisons may be more critical than between–group (inter–individual) comparisons. To achieve both comparisons, the trial within cohorts (TwiCs) study design, in which the intervention study is performed within a prospective observational cohort with regular measurements [35, 36], is considered more appropriate than conventional standard RCTs. The TwiCs study design allows for an evaluation of not only within–group changes and between–group differences but also the long–term effects of exercise training intervention, because regular measurements in the prospective cohort will be continued after the completion of the intervention period [37].

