### Sample size calculation

The sample size calculation for this clinical trial is based on a previous study that explored the impact of a 1–year structured rehabilitation program on kidney function decline among patients with CKD, using a small sample from a TwiCs study design [49]. According to this previous study, the annual slope of eGFR (mL/min/1.73 m²/year) was approximately + 2 in the intervention group and − 3 in the control group, indicating a between–group difference of approximately 5 units per year. Assuming a standard deviation of 8, a two–sided significance level of 0.05, and a statistical power of 0.80, a total of 84 participants would be required based on a two–sample t–test.

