### Statistical analysis

All analyses will be conducted based on the intention–to–treat (ITT) principle. Statistical significance is set at *P* < 0.05. Data are expressed as mean ± standard deviations, median [interquartile range], or frequency counts (%), as appreciate. Baseline group characteristics will be compared using one–way analysis of variance or the Kruskal–Wallis test for continuous variables and the chi–square test or Fisher’s exact test for categorical variables. The eGFR slope for the 6–year pre–intervention, 1–year during–intervention, and 1–year post–intervention phases will be calculated. For calculating the eGFR slope, the repeated measurements of eGFR will be analyzed using a linear mixed model (LMM) including continuous time as a fixed effect and individual participant as a random effect (henceforth, Model 1). In addition, the slope will be estimated using a single linear regression of eGFR on time by each participant (called as Model 2) as a supplementary analysis.

For a primary analysis, the eGFR slope will be compared using the LMM including the group (exercise, stretching, and usual lifestyle), time, their interaction term, and the baseline eGFR as fixed effects and individual participant as a random effect. The eGFR slopes calculated by Models 1 and 2 will also be compared between groups using analysis of covariance, including the group as a factor and the eGFR slope of the 6–year pre–intervention phase as a covariate. The eGFR slope for the 6–year pre–intervention, 1–year during–intervention, and 1–year post–intervention phases will be performed using paired t–tests for within–group comparison.

Secondary outcomes will be analyzed using the generalized estimating equations (GEE) method, including group, categorical time point (baseline, 6 months, and 1 year), and their interaction term as factors. In each model, an unstructured (UN) correlation matrix will be used to account for within–individual correlations across time points. If the UN matrix leads to a convergence problem for numerical optimization, a simpler correlation structure will be used. The results of the GEE analysis will be presented as the marginal means with 95% confidence intervals. Pearson product–moment correlation analysis and repeated–measure correlation analysis [50] will be conducted to examine the associations between individual changes in each outcome.

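### Random-intercept slope model: Model 1 gives every participant the same slope, so its ANCOVA cannot be run, and the primary group-by-time standard error is too small if true slopes vary and three or more visits enter

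*Protocol article*

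**What the plan says.** In the protocol article, Primary and secondary outcome measures defines the primary outcome as the annualized eGFR slope and fixes how it is obtained: "The eGFR slope is determined using a linear mixed–effects model with random intercepts".

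Statistical analysis describes three uses of slope models:

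- Model 1, the main slope calculation, is a "linear mixed model (LMM) including continuous time as a fixed effect and individual participant as a random effect". Model 2, a separate regression for each participant, is supplementary.
- The primary analysis is a mixed model whose terms are group and time, together with "their interaction term, and the baseline eGFR as fixed effects and individual participant as a random effect".
- Slopes from both calculations then go into a further comparison: "The eGFR slopes calculated by Models 1 and 2 will also be compared between groups using analysis of covariance", with the pre-intervention slope as covariate. The slopes of the three phases are also to be compared within groups; this "will be performed using paired t–tests for within–group comparison".

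No random slope, unstructured within-person covariance or robust standard error is named for the eGFR models. An unstructured correlation matrix is named only for the GEE analyses of secondary outcomes.

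The Introduction bases the design on the view that "kidney aging is irreversible and progresses slowly with significant individual variations".

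**The concern.** A random intercept lets participants differ in eGFR level but not in rate of change. Two consequences follow.

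First, the ANCOVA on Model 1 slopes needs one slope per participant for both outcome and covariate, and Model 1 does not supply them. The lead hypothesis in the Introduction, that decline during the intervention is slower than before it within the same exercise-group individuals, also needs individual slopes.

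Second, the primary group-by-time test assumes that everyone in a group shares one true slope, whereas the Introduction says that people vary. Real slope variation left out of the model is partly treated as independent visit-to-visit noise. The standard error of the slope difference then comes out too small, intervals are too narrow, and the 5% level is exceeded in the confirmatory test.

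**Working it through.** **The plan's own figure.** Sample size calculation assumes "indicating a between–group difference of approximately 5 units per year", an SD of 8, two-sided 0.05 and power 0.80. The normal approximation gives 2 × (1.96 + 0.84)² × 8² / 5² ≈ 40.2, so 41 per arm. The exact t-based calculation gives 42 per arm, 84 in total, with power 0.808. The stated 84 is reproduced. That calculation treats the slope as a participant-level quantity with total SD 8.

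**Model 1.** Write eGFR for person i at time t as (β0 + b_i) + β1·t + error. The person effect b_i enters the level only, so the fitted slope is β1 for every i. Fitting by phase gives one constant per phase, and fitting by group gives one constant per group. Either way the variance within a group is zero. The ANCOVA then has a constant covariate and no residual variance. A trial fit to simulated data agreed: one random term per participant (the intercept) and one slope for all.

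**Primary group-by-time test.** Inputs:

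- Visits at 0, 0.5 and 1 year (Measurements).
- Groups of 43, 45 and 53 (Table 1).
- Total SD of one-year slopes 8 (Sample size calculation).
- Share p of the slope variance that is truly between people: not given, so varied.

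Let τ² be the between-person slope variance, σ² the residual variance, k the number of visits and Sxx the sum of squared centred times. For balanced data, the variance of one person's estimated slope is

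- true: τ² + σ²/Sxx
- as used by the random-intercept model: τ²/(k − 1) + σ²/Sxx

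At 0/0.5/1, Sxx = 0.25 + 0 + 0.25 = 0.5 and k = 3. Setting τ² + 2σ² = 64 with τ² = 64p, the ratio of reported to true variance is [64(1 − p) + 32p]/64 = 1 − p/2. Type I error is 2 × [1 − Φ(1.96 × SE ratio)].

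| Share p | τ | σ | SE ratio √(1 − p/2) | Type I error |
|---|---|---|---|---|
| 10% | 2.53 | 5.37 | 0.975 | 5.6% |
| 25% | 4.00 | 4.90 | 0.935 | 6.7% |
| 50% | 5.66 | 4.00 | 0.866 | 9.0% |
| 75% | 6.93 | 2.83 | 0.791 | 12.1% |

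**Simulation check** (3,000 runs per setting, 43/45/53 participants, same four shares). Exercise versus stretching rejected in 5.4%, 6.0%, 9.2% and 12.9% of runs under the null. The three-group test rejected in 5.7%, 6.2%, 10.5% and 14.5%. A mixed-model fit with baseline eGFR as covariate at the 50% share gave 12% (150 runs only). A t-test on per-participant slopes stayed between 4.2% and 5.6% in every setting.

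**Dependence on the visits that enter.**

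- Two time points: k − 1 = 1, the two variance expressions coincide, and there is no inflation.
- One line through 0, 0.5, 1 and 2 years: Sxx = 2.1875 and k = 4. With the same τ and σ, the SE ratios are 0.884, 0.778, 0.676 and 0.617, and type I error is 8.3%, 12.8%, 18.5% and 22.7%.

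**The case against.** The strongest reply is that the outcome section does not say intercepts only, that the analysis section says merely that participant is a random effect, and that using Model 1 slopes in an ANCOVA makes sense only if they vary. On this view a random slope was intended and its detail belongs to the SAP. The intention is plausible. But the one place that names the random-effects structure names intercepts, and nothing names a random slope. The text as it stands fixes a model that contradicts its own use.

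Other parts of the reply stand and limit the point:

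- The inflation depends on an unstated variance share, and the SD of 8 is itself an assumption, set beside effects from a CKD study. The protocol describes its own participants as having relatively preserved kidney function. With true slope SDs of 1 to 3 and residual SDs of 4 to 5, the same formula at 0, 6 and 12 months gives only about 5.1% to 6.4%.
- Baseline eGFR is a covariate in the primary model. If baseline is not also an outcome value, only the 6- and 12-month values enter over the intervention year, and the inflation vanishes.
- The paired t-test sentence names no model. Those tests fail only if run on Model 1 slopes.
- An ANCOVA on Model 2 slopes is already planned, so a workable comparison of individual slopes exists, though as a supplementary analysis.

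A reader might infer far larger inflation by imagining the primary model as one straight line through the pre-intervention cohort years and the trial visits. The protocol does not support that: slopes are calculated separately by phase, and the primary model adjusts for baseline eGFR. Nor does it state that a single line to 24 months, across the end of the intervention, will be fitted. The four-visit figures show sensitivity and do not describe the plan.

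**Conclusion.** The point holds in two parts of different strength.

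The first follows from the stated model without numerical assumptions: random-intercept Model 1 slopes have no variance between participants, so the ANCOVA on them cannot be run as written. The same applies to the paired t-tests if they use Model 1.

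The second is certain in direction but conditional. It needs true slope variation, which the Introduction asserts, and at least three time points in the model. Under those conditions, over 12 months with a total slope SD of 8, type I error runs from just above nominal at a 10% between-person share to about 12% at 75%. The document does not settle where in that range the trial lies. It would be wrong to infer that the trial lacks any sound slope analysis, since Model 2 provides one. What needs correcting is the rank given to each model and the error structure of the primary test.

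**What to change.** Before outcome data are analysed:

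1. Specify a random intercept and a random slope for time in the primary mixed model and in Model 1. State the fallback if the model does not converge: cluster-robust standard errors, or a comparison of per-participant slopes.
2. State which visits enter the primary model, and whether baseline eGFR is an outcome value as well as a covariate.
3. Run the ANCOVA and the paired t-tests only on slopes that can differ between participants (Model 2 slopes or random-slope estimates), and name the model in the paired-test sentence. Random-slope estimates from a model without group terms are shrunk toward a common slope, so Model 2 slopes are the simpler choice for these comparisons.
4. Make the wording on random effects agree between the outcome and analysis sections.

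This changes analysis wording only and needs no new data. Intervals become somewhat wider: at the 12-month shares above, by 1/0.975 to 1/0.791, about 3% to 26%. With so few visits per participant the random slope may be poorly estimated or fail to converge, which is why the fallback is needed. The sample size of 84 is unchanged, because it already rests on the total SD of individual slopes.

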### Assessment of adverse events and adherence

Adverse events will be monitored continuously throughout the study period via monthly participant check–ins, standardized questionnaires, and review of training logs. All reported adverse events will be categorized systematically, with serious adverse events being promptly reviewed by independent clinical advisors. Serious adverse events will be classified if they result in death, are immediately life–threatening, require inpatient hospitalization, or lead to persistent or significant disability/incapacity. Affected participants are free to discontinue the trial or continue with the intervention. Adherence to the intervention, including the frequency and intensity of exercise and stretching (both supervised and home–based), throughout the 12–month intervention period will be assessed using a self–recorded exercise and stretching diary. If a participant drops out of the intervention program, the reasons will be recorded.

### Sample size calculation

The sample size calculation for this clinical trial is based on a previous study that explored the impact of a 1–year structured rehabilitation program on kidney function decline among patients with CKD, using a small sample from a TwiCs study design [49]. According to this previous study, the annual slope of eGFR (mL/min/1.73 m²/year) was approximately + 2 in the intervention group and − 3 in the control group, indicating a between–group difference of approximately 5 units per year. Assuming a standard deviation of 8, a two–sided significance level of 0.05, and a statistical power of 0.80, a total of 84 participants would be required based on a two–sample t–test.

### Statistical analysis

All analyses will be conducted based on the intention–to–treat (ITT) principle. Statistical significance is set at *P* < 0.05. Data are expressed as mean ± standard deviations, median [interquartile range], or frequency counts (%), as appreciate. Baseline group characteristics will be compared using one–way analysis of variance or the Kruskal–Wallis test for continuous variables and the chi–square test or Fisher’s exact test for categorical variables. The eGFR slope for the 6–year pre–intervention, 1–year during–intervention, and 1–year post–intervention phases will be calculated. For calculating the eGFR slope, the repeated measurements of eGFR will be analyzed using a linear mixed model (LMM) including continuous time as a fixed effect and individual participant as a random effect (henceforth, Model 1). In addition, the slope will be estimated using a single linear regression of eGFR on time by each participant (called as Model 2) as a supplementary analysis.

For a primary analysis, the eGFR slope will be compared using the LMM including the group (exercise, stretching, and usual lifestyle), time, their interaction term, and the baseline eGFR as fixed effects and individual participant as a random effect. The eGFR slopes calculated by Models 1 and 2 will also be compared between groups using analysis of covariance, including the group as a factor and the eGFR slope of the 6–year pre–intervention phase as a covariate. The eGFR slope for the 6–year pre–intervention, 1–year during–intervention, and 1–year post–intervention phases will be performed using paired t–tests for within–group comparison.

Secondary outcomes will be analyzed using the generalized estimating equations (GEE) method, including group, categorical time point (baseline, 6 months, and 1 year), and their interaction term as factors. In each model, an unstructured (UN) correlation matrix will be used to account for within–individual correlations across time points. If the UN matrix leads to a convergence problem for numerical optimization, a simpler correlation structure will be used. The results of the GEE analysis will be presented as the marginal means with 95% confidence intervals. Pearson product–moment correlation analysis and repeated–measure correlation analysis [50] will be conducted to examine the associations between individual changes in each outcome.

As a sensitivity analysis, multiple imputations will be applied to the missing outcome data to assess the robustness of the findings from the above analyses. In addition, pre–specified subgroup analyses based on baseline characteristics will be performed to further explore potential effect modification. Specifically, subgroup analyses will be conducted according to baseline kidney function (eGFR < 60 mL/min/1.73 m²), glycemic control status (hemoglobin A1c ≥ 6.5%), hypertension status (systolic blood pressure ≥ 140 mmHg and/or diastolic blood pressure ≥ 90 mmHg), and obesity/overweight (body mass index ≥ 25 kg/m²).

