This study has several limitations that should be considered when interpreting our findings. First, due to the voluntary selection of participants into either the intervention or usual lifestyle groups before randomization, there may be potential selection bias; participants opting into intervention groups could systematically differ in baseline health status compared to those choosing the usual lifestyle group. However, as shown in Table 1, the baseline characteristics of exercise, stretching, and usual lifestyle groups were generally comparable, with no substantial differences observed among the three groups. The second concern is the risk of participant dropout. The previous study has shown a completion rate of 80% [49], but this may be optimistic. The extent of dropout could affect the generalizability of the results. To address this concern, we plan to conduct sensitivity analyses to examine the robustness of our findings. Third, the risk of type I error is increased due to the presence of multiple secondary endpoints because the multiplicity of test for the endpoints will not be controlled. Therefore, results from the secondary analyses will be interpreted cautiously and viewed primarily as hypothesis–generating rather than confirmatory. Fourth, in participants with early diabetes or pre–diabetes, transient glomerular hyperfiltration could temporarily elevate eGFR, thereby masking initial declines in kidney function. To mitigate this issue, subgroup analyses stratified by baseline glycemic control status using hemoglobin A1c thresholds (e.g., ≥ 6.5%) will be conducted. Finally, it is important to note that our participants have relatively preserved kidney function compared to populations studied in previous CKD trial [49]; hence, the magnitude of exercise–induced benefits observed in prior CKD–specific studies might not directly generalize to our study population.

In summary, this study is the first long–term RCT in the field of sports nephrology to employ the TwiCs study design. In the context of an ultra–aged society in which the prevalence of CKD is expected to continue to rise, our study provides crucial clinical and physiological insights into the role of regularly performed exercise as a primary prevention for CKD in middle–aged and older adults.

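### The per-participant slope ANCOVA and the paired t-tests use only participants with enough eGFR values in each phase, so they are observed-data analyses and should not carry the ITT label

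*Protocol article*

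**What the plan says.** The Statistical analysis section of the protocol article opens with a blanket statement: "All analyses will be conducted based on the intention–to–treat (ITT) principle". It then sets out several analyses of eGFR slope:

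- **Primary, between groups.** "For a primary analysis, the eGFR slope will be compared using the LMM including the group (exercise, stretching, and usual lifestyle), time, their interaction term", with baseline eGFR as a further fixed effect and the participant as a random effect.
- **Model 2.** "the slope will be estimated using a single linear regression of eGFR on time by each participant (called as Model 2", described there "as a supplementary analysis".
- **ANCOVA on slopes.** "The eGFR slopes calculated by Models 1 and 2 will also be compared between groups using analysis of covariance", with the pre-intervention slope as covariate. No weighting is stated.
- **Within groups.** The slopes of the pre-, during- and post-intervention phases "will be performed using paired t–tests for within–group comparison".

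Under Primary and secondary outcome measures, the model that yields the slope has intercepts as its only random effect: "The eGFR slope is determined using a linear mixed–effects model with random intercepts".

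The Measurements section sets visits at 0, 6, 12 and 24 months. The paragraph after the main analyses plans multiple imputation of missing outcomes as a sensitivity analysis. The Discussion says of dropout: "The previous study has shown a completion rate of 80% [49], but this may be optimistic".

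Hypothesis 1, in the Introduction, is a within-person comparison. It expects eGFR decline in the exercise group to be slower during the intervention year than before it.

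**The concern.** A slope fitted to one participant's values needs at least two values in the phase. A participant without them cannot enter the ANCOVA or the paired t-test, and nothing in the main specification puts that participant back. A participant with only the first half of the intervention year does enter, with a slope annualised from two values six months apart and counted the same as a full-year slope. An analysis limited in this way is one of observed data, which does not fit a statement that every analysis is ITT.

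The label matters most for the paired t-test. It is the only stated test of hypothesis 1, and the Introduction suggests that within-group comparisons may matter more than between-group ones. The article does not say which model supplies its slopes. However, a model with random intercepts only gives no participant-specific slopes, so in practice the test has to rest on Model 2.

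**Working it through.** **1. The plan's own figure.** Sample size calculation: difference 5, SD 8, two-sided 0.05, power 0.80, two-sample t-test. The exact t-test needs 41.17 per arm, so 42 per arm and 84 in total. The stated 84 is reproduced. The SD of 8 is used in step 3.

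**2. Who has a slope, and how precise it is.** Let s be the within-person SD of eGFR. The residual variance of a fitted slope is s²/Sxx, where Sxx = Σ(t − mean t)² and t is in years.

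| eGFR values available | Sxx | Residual variance of slope |
|---|---|---|
| 0, 6, 12 months | 0.25 + 0 + 0.25 = 0.5 | 2s² |
| 0, 6 months | 0.0625 + 0.0625 = 0.125 | 8s² |
| 0 only | 0 | no intervention-phase slope |
| 12, 24 months | 0.25 + 0.25 = 0.5 | 2s² |
| 12 or 24 missing | 0 | no post-phase slope |

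The ratio 8/2 = 4 does not depend on s.

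**3. Size of s (assumption).** The article gives no within-person SD. If the planned SD of 8 is the total SD of a completer's slope, then 2s² ≤ 64, so s ≤ 5.66. Taking s from 4 to 5.66, the residual SD of the slope is √2·s = 5.7 to 8.0 for completers and √8·s = 11.3 to 16.0 for those with 0 and 6 months only.

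**4. Precision in one arm (illustrative split).** Take an arm of 44 with about 20% loss: 4 with baseline only, 5 with 0 and 6 months, 35 complete.

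- Sum of residual variances: 35×2 + 5×8 = 110 (units of s²). The 5 are 5/40 = 12.5% of slopes and 40/110 = 36% of residual variance.
- Variance of the unweighted mean: 110/40² = 0.0688s².
- Completers only: 2/35 = 0.0571s².
- Inverse-variance weights: 1/(35/2 + 5/8) = 0.0552s².

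On residual variance alone, the unweighted standard error is √(0.0688/0.0571) = 1.10 times that of completers only. True variation in slope between people, with variance τ², reverses the order only if τ² exceeds (0.06875 − 0.05714)/(1/35 − 1/40) = 3.25 times s². With τ² + 2s² = 64, that needs s below √(64/5.25) = 3.5.

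**5. A level shift.** Suppose eGFR rises by 2 by month 6 and then holds. A completer's slope is +2. Someone with 0 and 6 months only has 2/0.5 = +4. The arm mean is (35×2 + 5×4)/40 = 2.25, a shift of 0.25, or 5% of the planned difference of 5.

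**6. Bias under outcome-dependent loss (simulation, assumed inputs).** Arms of 43 and 45, true slopes +2 and −3, within-person SD 5, between-person slope SD 2, 10% with baseline only, 300 runs. The comparison is of unadjusted mean Model 2 slopes with a random-intercept mixed model.

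| Loss after month 6 | Model 2 | Mixed model |
|---|---|---|
| 11% of the rest, unrelated to eGFR | 5.11 (SD 1.86) | 5.12 (SD 1.76) |
| Exercise arm only: 30% of those whose eGFR fell by month 6 | 3.76 (SD 1.91) | 5.08 (SD 1.79) |

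The Monte Carlo error of each mean is at most about 1.91/√300 = 0.11. In the first row neither method is biased and Model 2 is slightly less precise. In the second, Model 2 is 5 − 3.76 = 1.24 too low and the mixed model is not. About 79 of 88 participants had a Model 2 slope.

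**The case against.** The other side has a good deal of substance.

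- **The primary analysis does not have this fault.** The group-by-time mixed model works on the repeated eGFR values and gives partial records the weight their information supports. Model 2 is openly called supplementary. This stands.
- **Imputation is planned.** It covers the analyses described before it, which include the ANCOVA and the paired t-tests, and it could complete every slope. This stands as mitigation. Because it is a sensitivity analysis, the main versions of these tests still rest on observed data.
- **ITT can be read loosely**, as analysing people as randomised on the data available. That reading is common. It makes the point one of labelling, but it does not change who is left out.
- **Leaving the programme is not losing eGFR.** The adverse events section treats stopping the intervention and leaving the trial as different things, and cohort measurement continues. Only missing eGFR values count here.
- **The effect may be small.** In the level-shift example it is 0.25 against a planned 5.

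Two stronger readings are tempting. A reader might infer that the trial's main between-group result is not ITT. The documents do not support that, for the first reason above. A reader might also infer that withdrawals necessarily distort these tests or are over-counted. Each participant counts once, and loss unrelated to eGFR costs precision only.

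**Conclusion.** The point holds in a limited form. The Model 2 ANCOVA and the paired t-tests on phase slopes are observed-data analyses under an ITT label.

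- **Certain from the visit schedule.** In the randomised arms, a baseline-only participant has no intervention-phase slope. A participant without the 12- or 24-month value has no post-phase slope. A slope from 0 and 6 months has four times the residual variance at equal weight. If the usual lifestyle group is seen only yearly, as its own section suggests, anyone there without a 12-month value has no intervention-phase slope.
- **Dependent on assumptions.** The precision loss is about 10% in the standard error for the split shown. A bias of about 1.2 out of 5 arises only in a scenario where loss depends on the month-6 value. That scenario shows what can happen and is not a forecast. The mixed model's advantage assumes that loss depends on observed values only.

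This is a minor point. It deserves attention because the affected paired t-test carries hypothesis 1.

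**What to change.** 1. In Statistical analysis, limit the ITT statement so that it no longer covers the Model 2 ANCOVA and the paired t-tests. Describe those as supportive analyses of participants with the eGFR values needed in each phase.
2. Base the hypothesis 1 conclusion on one mixed model of all eGFR values, with separate slopes before, during and after the intervention and random intercepts and slopes for participants. The estimate of interest is the during-minus-before slope in the exercise group. Keep baseline eGFR as an outcome value, so that a participant with no later value still contributes. The paired t-test can stay as support.

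The cost is a few sentences and a little more modelling. The downside is that the supportive tests carry a weaker label. No visit, measurement or sample size changes.
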